**ELECTRIC specific treatment related expected adverse events:**

In this trial the following related minor AEs are potentially expected:

- Transient skin redness at electrodes sites
- Minor itch at electrode sites

There are no related serious AEs expected in this trial.

**7.3 Procedures for detecting, recording, evaluating & reporting AEs, SAEs**

**7.3.1 Detecting AEs and SAEs**

All AEs and SAEs meeting the criteria for recording within the ELECTRIC trial (see section 7.2) are recorded, from the time a participant consents to join the trial until the last trial follow-up. The RRA asks the participant/proxy (consultee [England], welfare attorney/nearest relative [Scotland]) or CH staff delivering the TPTNS/sham intervention about the occurrence of relevant AEs (i.e. those that meet the criteria for recording within the ELECTRIC trial) at each follow-up data collection point. AEs are also recorded in the stimulation diary.

**7.3.2 Recording AEs and SAEs**

When an AE/SAE meeting the criteria for recording within the ELECTRIC trial occurs, it is the responsibility of the local PI / RRA (or delegate) to review CH documentation related to the event. The local PI /RRA then records all relevant information about AEs in the relevant safety form. If an AE/SAE is recorded, the Trial Office liaises with the local PI /RRA to obtain further information if appropriate.

**7.3.3 Evaluating AEs and SAEs**

Seriousness, relatedness (causality), and expectedness is evaluated by a registered healthcare professional, including the local PI / RRA / CI

### *Assessment of Seriousness*

### The local PI / RRA / CI will make an assessment of seriousness as defined above.

### *Assessment of Relatedness (causality)*

The CI / RRA will make an assessment of whether the AE is likely to be related to research procedures according to the following definitions:

- **Related**: resulted from administration of TPTNS or sham stimulation or the outcomes data collection processes.
- **Unrelated**: where an event is not considered to have resulted from any of the research procedures.

Alternative causes such as natural history of any underlying disease, concomitant therapy, other risk factors and the temporal relationship of the event to the treatment are considered.

### *Assessment of Expectedness*

When assessing expectedness refer to the expected events (Section 7.2).

**7.3.4 Notification and reporting AEs and SAEs**

CH local PIs / RRAs are responsible for notifying the Trial Office of any AEs and SAEs meeting the criteria for recording within the ELECTRIC trial.

If an SAE form is submitted to the Trial Office, the Trial Manager is automatically notified. If, in the opinion of the local PI and/or the CI, the event is confirmed as being *serious* and *related* and *unexpected*, the CI or Trial Manager notifies the Sponsor within 24 hours of receiving the signed SAE notification. The Sponsor provides an assessment of the SAE. A Sponsor cannot downgrade an assessment from the PI or CI. Any disparity is resolved by further discussion between these parties. If all the required information is not available at the time of reporting, the local PI / RRA must ensure that any missing information is provided as soon as this becomes available. It should be indicated on the report that this information is follow-up information of a previously reported event.

**7.3.5 Regulatory reporting requirements**

The CI or delegate reports any SAEs that are related to any of the research procedures and unexpected to the appropriate REC (Scotland or England) within 15 days of the CI becoming aware of it using the HRA SAE form.

The CI is responsible for submitting annual reports to each REC on the anniversary of the approval. All related SAEs are summarised and reported to the Ethics Committee, the Funder, the Trial Steering Committee and the Data Monitoring Committee in their regular reports.

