**4.7 Methods to protect against other sources of bias**

*Attrition*: The major anticipated source of attrition is resident death. Reasons for attrition are accurately recorded in each CH and therefore there should be minimal actual loss of residents to follow up at 18 weeks. Anticipated mortality rates have been accounted for in the sample size calculation and analysis plan.

*Use of sham stimulation as control*: To ensure the resident and their relatives are blind to the allocated intervention group a sham stimulation intervention rather than a no-treatment control is used.

*Contamination:*The risk that residents may receive the alternative intervention to which they were randomised will be addressed by the Implementation Support Facilitator, who will check digital photographs of electrode position taken by delivering nurses/senior carers on a bi-weekly basis and correct any delivery fidelity breach, including checking the stimulation diaries recorded after each session to ensure the information aligns with the allocated group. In addition, the electrical stimulator information downloads will be undertaken bi-weekly and will indicate any delivery protocol breaches, by comparing recorded parameters against the expected.

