## 7. SAFETY

**7.1 Standard definitions**

An **adverse event** (AE) is any untoward medical event affecting a clinical trial participant. Each initial AE is considered for severity, causality or expectedness and may be reclassified as a serious adverse event based on prevailing circumstances.

A **serious adverse event** (SAE), is any AE, that:

- results in death;
- is life threatening (i.e. the subject was at risk of death at the time of the event; it does not refer to an event which hypothetically might have caused death if it were more severe);
- requires hospitalisation or prolongation of existing hospitalisation;
- results in persistent or significant disability or incapacity;
- is otherwise considered medically significant by the investigator.

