***7.2 Trial specific considerations***

In this trial, all AEs occurring during an electrical stimulation (treatment/sham) session, or while equipment is attached to the resident’s leg, or during data collection periods are recorded eg during questionnaire completion, interviews or 24-hour pad collections (see definitions below). Given the previous established safety profile of the TPTNS, serious related AEs are not anticipated in this low-risk trial. However, any serious related AEs that do occur will be recorded as such.

Hospitalisations for elective treatment of a pre-existing condition are not considered as an AE or SAE. Complications occurring during such hospitalisation are also not AEs or SAEs.

Falls, fractures, UTIs, emergency admissions to hospital in 6-month period prior to the resident’s participation in the ELECTRIC trial are recorded at study baseline. Falls, fractures and emergency admissions to hospital are not considered as related AEs/SAEs during the trial period unless they occur during a treatment session or during the measurement of study outcomes. Symptomatic UTIs treated with antimicrobials occurring at any time during the resident’s 18-week participation period, are considered to be AEs/SAEs.

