## 9. SAMPLE SIZE AND PROPOSED RECRUITMENT RATE

**9.1 Sample size**

A total of 500 residents will be required for this study, recruited across the two regions in accordance with allocation of RRA resources in that region. The worthwhile difference we believe the intervention will result in is a reduction of 200ml/24 hours. There is a lack of data available on the potential standard deviation of Pad Weight Tests37 (PWT) in CH residents; however, a small RCT2 reported results on this outcome. The SD from the trial was about 450ml, but given the small and selected sample included we estimated the upper 95% confidence interval around the SD which was approximately 570ml/24 hours, hence the standardised effect size of 0.35 (i.e. 200/570). To detect that difference with 90% power at the two-sided 5% alpha level we need primary outcome data on 344 participants. The limited data available suggested that the intra-class correlation (ICC) for any possible clustering effect was likely to be negligible; however, we have inflated this number to 500 to cover a conservative estimate of attrition to the primary outcome of about 30% due to death of CH residents and potential transfers to other CHs.

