**12.5 Data Monitoring Committee (DMC)**

An independent Data Monitoring and Ethics Committee (DMEC) oversee the safety of subjects in the trial. The DMEC Charter documents the terms of reference of the DMEC and the names and contact details and is filed in the TMF. The Committee meets regularly to monitor the trial data and make recommendations as to any modifications that are required to be made to the protocol or the termination of all or part of the trial. CHaRT has adopted the DAMOCLES Charter for DMECs.

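### The SAE recording and reporting rules screen out most deaths twice, and the protocol does not require that all-cause deaths by arm go to the DMEC

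*Protocol*

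**What the plan says.** Section 7.1 of the protocol counts as serious any adverse event that "results in death". Section 7.2 then narrows what is recorded to "all AEs occurring during an electrical stimulation (treatment/sham) session", or while equipment is attached to the leg, or during data collection. Symptomatic UTIs treated with antimicrobials are added at any time in the 18 weeks. Section 7.3.1 repeats the limit: "All AEs and SAEs meeting the criteria for recording within the ELECTRIC trial (see section 7.2) are recorded". Section 7.2 also states: "Falls, fractures and emergency admissions to hospital are not considered as related AEs/SAEs during the trial period unless they occur during a treatment session", with a further exception for events during outcome measurement.

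For routine reporting, section 7.3.5 says: "All related SAEs are summarised and reported to the Ethics Committee, the Funder, the Trial Steering Committee and the Data Monitoring Committee". Section 7.2 lists no related serious event as expected.

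Elsewhere, section 12.5 has the DMEC "oversee the safety of subjects in the trial" and monitor trial data under a charter held in the trial master file. Section 10.1 gives it confidential interim analyses at least annually. Deaths are treated as loss to follow-up. Section 4.7 says: "The major anticipated source of attrition is resident death". Section 9.1 allows for "attrition to the primary outcome of about 30% due to death of CH residents" and for transfers to other homes. Reasons for attrition are recorded (section 4.7), and death is one of the changes of status in section 6.5.

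**The concern.** In a frail population a single death will seldom be attributed to low-current stimulation of the ankle. A harm that nobody expected would show, if at all, as a difference in counts between the randomised arms, and that comparison needs no causality judgement on individual cases. The written rules put two filters ahead of it. An event must first fall within a narrow window to be recorded, and it must then be judged related to enter the routine report. The most frequent serious outcome the protocol anticipates could be almost wholly missing from the one safety report whose content the protocol specifies.

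What is at stake is whether the committee charged with participant safety is sure to be shown the mortality balance, or sees it only if the charter provides for it or the committee asks.

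**Working it through.** **1. The plan's own figures.** With a standardised effect of 0.35, 90% power and two-sided 5% alpha, n per arm = 2 × (1.960 + 1.282)² / 0.35² = 171.6, so 172 per arm and 344 in total, as section 9.1 states. Allowing 30% loss, 344 / 0.70 = 492, which is close to the planned 500. The allowance is therefore up to 0.30 × 500 = 150 residents without primary outcome data, from death and transfer together. The protocol gives no split.

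**2. The path of a death through the safety rules.**

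| Step | Section | Effect on a death between sessions |
| --- | --- | --- |
| Definition | 7.1 | Is an SAE |
| Recording | 7.2, 7.3.1 | Need not be recorded, unless it arises from a treated symptomatic UTI |
| Relatedness | 7.3.3 | Assessed only if recorded |
| Routine report | 7.3.5 | Included only if judged related |
| Attrition and status records | 4.7, 6.5 | Captured, but not linked to any safety report |

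**3. How narrow the recording window is.** Follow-up is 18 × 7 × 24 = 3,024 hours. Stimulation takes 12 × 0.5 = 6 hours. Three 24-hour pad collections take 72 hours. That makes 78 / 3,024 = 2.6% of follow-up. If the three 24-hour bladder diaries were kept on separate days, the figure is 150 / 3,024 = 5.0%. Questionnaire and interview time would add to this, but its length is not stated. If deaths are spread roughly evenly over follow-up (an assumption), most fall outside the window.

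**4. What the report could miss (assumed counts, 250 per arm).** With 45 v 25 deaths (18% v 10%) the difference is 0.08, with SE = √(0.18 × 0.82/250 + 0.10 × 0.90/250) = 0.0308. The 95% CI is 0.08 ± 1.96 × 0.0308, or 2.0 to 14.0 points; Fisher's exact p = 0.014. With 50 v 30 deaths, p = 0.020. If every such death is either unrecorded or judged unrelated, the section 7.3.5 report shows 0 v 0 in both cases.

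**5. What tabulation could show.** Two-sided 5% power for two proportions is Φ[(d − 1.96 × SE₀)/SE₁], with SE₀ pooled and SE₁ unpooled. For 10% v 15%, SE₀ = 0.0296 and SE₁ = 0.0295, so power = Φ[(0.05 − 0.0580)/0.0295] = 39%. The control mortalities below are assumed.

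| Control mortality | Deaths in 250 | Power, risk × 1.5 | Power, risk × 2 |
| --- | --- | --- | --- |
| 5% | 12.5 | 21% | 57% |
| 10% | 25 | 39% | 88% |
| 20% | 50 | 73% | over 99% |

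A by-arm table would usually reveal a doubling of mortality unless mortality is low. A 1.5-fold increase would often not reach significance.

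**The case against.** The strongest reply is that section 7.3.5 sits under regulatory reporting and states what goes into certain regular reports; it does not say that the committees receive nothing else. Section 10.1 gives the DMEC interim analyses at its discretion and at least annually. Section 12.5 has it monitor trial data and recommend changes or termination. Death is recorded trial data, and report tables commonly sit in a charter, which is not shown. Section 10.1 also describes safety data at the end of the trial without a relatedness limit and requires reporting to CONSORT.

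Most of this stands. A reader might infer that the DMEC is sent only related SAEs and that an excess of deaths in one arm would go unseen. The documents do not support that: the DMEC has wider access, and the charter may list deaths. A reader might also infer that the trial sets out to conclude that the treatment is safe. No aim, objective or outcome in sections 2 and 5 says so; safety is presented as already established.

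What the reply does not remove is that the protocol makes one explicit rule about the safety content of committee reports, that this rule is filtered by causality, and that no section says deaths by arm are shown. The end-of-trial safety description can also draw only on what section 7.2 lets in, unless deaths are added from the attrition records.

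**Conclusion.** The point holds in a limited form. The written SAE rules exclude most deaths, first by when they occur and then by judged relatedness, although death meets the protocol's own SAE definition and is its main anticipated cause of loss. The DMEC may see deaths by another route, but the protocol does not require it.

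The size cannot be fixed from the document. Up to about 150 residents are allowed for as lost to death and transfer combined, and the death counts and mortality rates in the working are assumptions. That most deaths fall outside the window rests on their being spread over follow-up. Tabulating deaths would not guarantee detection of a moderate imbalance, but it would put the randomised comparison before the committee. The change is worth making because the data are already collected.

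**What to change.** In section 7.3.5, reconciled with 7.1, 7.2 and 12.5, state that:

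- the DMEC's confidential report tabulates by arm all deaths from any cause, taken from the attrition and change-of-status records (sections 4.7 and 6.5), together with all recorded AEs and SAEs regardless of judged relatedness;
- the TSC receives the pooled totals;
- the by-arm table appears in the final safety results.

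Deleting the word 'related' from section 7.3.5 would not be enough, because deaths outside the section 7.2 windows would still be missing from the SAE data. Expedited reporting to the Sponsor and the RECs stays as it is.

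The cost is a sentence or two in the protocol and one additional table, with no new data collection. The drawback is a slightly longer closed report containing many background deaths.

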## 8. EMBEDDED QUALITATIVE WORK

#### *8.1 Overview*

The longitudinal process evaluation is undertaken concurrently with the RCT. The objectives are:

- To explore the experiences of the TPTNS intervention from the perspectives of residents, family carers and care home staff.
- To explore factors affecting intervention implementation in the care home context and optimisation for sustainability.

#### 8.2 Data collection

*Qualitative interviews:* Interviews are undertaken by a research assistant skilled in the application of qualitative methods and will explore experiences of TPTNS or sham stimulation and any perceived impact on continence status and quality of life from the perspective of the CH residents and their family carers. Attention will be given to understanding the intervention acceptability in the short and longer term, especially in comparison to other UI management strategies they may be familiar with and the identification of potential adherence moderating factors for future TPTNS delivery. All interviews will be digitally recorded and transcribed verbatim in preparation for analysis.

*Resident and/or family carer interviews*: Face to face semi-structured interviews will be undertaken with residents and/or family carers, either as individual interviews or dyads. A total of 20 interviews will be carried out at 6 weeks, on completion of the intervention. A maximum of 20 further interviews with different residents/carers will take place at the 12-week juncture. Purposive sampling of resident/carers for the qualitative interviews will be undertaken on the basis of maximum variability sampling43 with regard to gender, age, bladder symptoms, cognitive and functional status and resident or carer status. Three quarters of the interviews will involve residents who have received the TPTNS intervention or their families. A topic guide for the semi-structured approach will be developed to ensure all questions of interest are addressed. Fewer interviews will be conducted if data saturation is reached.

*CH nurses/senior carer interviews*: Focus group (or small group) interviews will be undertaken with CH nurses and senior carers involved in the direct delivery of the TPTNS/sham intervention. Attention will be paid to understanding the organisation of care, how management works with care staff, level of staff turnover in the previous six months and how continence care is organised within the routines of the care home. One focus group per CH or where for staffing reasons this is not possible to organise, 2-3 small group interviews, will be held during the month following the intervention completion. This will result in the equivalent of 20 focus group interviews involving 60-100 CH staff. Additionally, up to 20 individual interviews will be undertaken with nurses/senior carers delivering the intervention, to explore and elicit views which staff may be reluctant to share in a group interview.

*CH Managers:* Individual telephone interviews with CH managers (n = 20) will be completed at the end of each CH’s involvement with the study (6 months following site inception). The focus of these interviews will be to explore the CH culture and management values, perceived effects of the continence intervention at the organisational level, including any impact on culture and quality of care and any economic effects. Strategic considerations for implementation rollout and sustainability in the event that TPTNS is found to be effective will be identified and explored in depth.

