**Recruitment of family carers**

Family members of participating residents who lack capacity to consent to participate in an interview are provided with study information by the local PI. Further explanation and the opportunity to ask questions about the study are offered to them by the RRA to enable an informed decision to be made about participation. Written consent to participate in the process evaluation interview is sought from the individual family carer prior to them taking part.

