**4.5 Randomisation and allocation**

Following consent, baseline data will be collected. Only once all baseline data are recorded will remote randomisation be initiated. Eligible and consenting residents are randomised to one of the two groups (TPTNS or sham) using the proven 24-hour telephone Interactive Voice Response randomisation application or via the web-based application (and phone, if appropriate), both hosted by CHaRT. Information required to perform the randomisation is submitted by the RRA, who has obtained the consent, however to ensure the RRA is blinded to group allocation the information on the allocated group is delivered to the local PI in each CH by the ELECTRIC trial office, who receive the allocation information from CHaRT. The local PI records the allocated group in a separate file and informs the CH staff who will deliver the allocated intervention.

Randomisation will be computer allocated on a one to one basis in random permuted blocks of size two, four or six, with stratification by:

- Sex – male/female
- UI severity - mild (0-200ml/24 hrs); moderate (200-400ml /24 hrs); severe (400+ ml/24 hrs)
- Centre

**4.6 Administration arrangements post recruitment** (if applicable)

Following recruitment, the following administration arrangements will be undertaken:

- The Trial Office will notify the resident’s GP/medical practitioner in writing that the resident has joined the trial.
- The RRA will file a copy of the consent form in the resident’s care notes along with information about the trial.
- The RRA will file a copy of the GP/medical practitioner letter in the resident’s care notes.
- The RRA will enter trial data regarding the resident into the bespoke trial website.
- The RRA will maintain trial documentation at each site in their region (Scotland or England).
- The RRA will return a copy of the signed consent form to the Trial Office in Glasgow.

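### Interviewees are picked partly by arm during follow-up, and nothing stops the blinded RRA, who explains the interview to some family carers, from learning who was picked

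*Protocol*

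**What the plan says.** **Interview sampling and timing (section 8.2).** The first round has a fixed size: "A total of 20 interviews will be carried out at 6 weeks, on completion of the intervention". The second round is capped at the same number and held with other people at week 12. Sampling is purposive, for maximum variability "with regard to gender, age, bladder symptoms, cognitive and functional status and resident or carer status". Treatment arm is not in that list, but the next sentence adds it as a quota: "Three quarters of the interviews will involve residents who have received the TPTNS intervention or their families". The number falls if saturation is reached. "Interviews are undertaken by a research assistant skilled in the application of qualitative methods"; section 12.1 places the qualitative researcher in the Trial Office.

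**Who approaches interviewees (section 4.4, Recruitment of family carers).** For residents who cannot consent to an interview, the local PI gives the family the information. Then: "Further explanation and the opportunity to ask questions about the study are offered to them by the RRA". Written consent follows, but the section does not say who takes it, or whether all such families or only selected ones are approached. No separate interview-recruitment step is described for residents with capacity.

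**Blinding (sections 4.5 and 4.7).** Allocation goes from the Trial Office to the local PI "to ensure the RRA is blinded to group allocation". The sham is used "To ensure the resident and their relatives are blind to the allocated intervention group".

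**Who measures outcomes (section 6.1 and Table 1).** The RRA weighs the pads, and is listed for the pad count, PVRU, PPBC, both MTSQ versions, DEMQOL and DEMQOL-proxy. Outcomes are taken at weeks 6, 12 and 18, with the DEMQOL measures at weeks 6 and 18 only.

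**The concern.** Allocation is 1:1, so before any interview the RRA has no better than an even guess at a resident's arm. A 3:1 quota makes selection for interview informative about arm. Section 4.5 takes trouble to route allocation around the RRA, yet section 4.4 puts the same person into one of the interview-recruitment steps while that resident's outcomes are still being collected.

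At stake is the assessor blind for the remaining measures of the interviewed residents. The questionnaires completed with the RRA present are the most open to influence, and the pad weight the least.

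**Working it through.** The protocol derives no figure on this point, so the check sets its counts against the allocation ratio and then asks which route could carry the information to the RRA.

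**Inputs**
- Interviews: 20 at week 6, at most 20 at week 12, with different people (section 8.2)
- TPTNS share of interviews: 0.75 (section 8.2)
- Residents: 250 per arm, allocated 1:1 (sections 3 and 4.5)
- Yardstick for the pad test: 200 ml/24 h; 344 residents needed with primary data (section 9.1)
- Assumptions: one distinct resident per interview, all 40 interviews held, and every selection known to an RRA who also knows the ratio. Together these give an upper bound.

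**Numbers exposed**
- All interviews: 0.75 × 40 = 30 TPTNS and 10 sham; 40/500 = 8% of residents
- By arm: 30/250 = 12% against 10/250 = 4%
- Week-6 interviews alone: 15 TPTNS and 5 sham; 20/500 = 4%

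**Information carried**
- P(TPTNS | interviewed) = 30/40 = 0.75, against 0.50 before
- P(TPTNS | not interviewed) = (250 − 30)/(500 − 40) = 220/460 = 0.478
- Odds ratio for TPTNS, interviewed against not: (30/220)/(10/240) = 3.3
- Guessing TPTNS for interviewees and sham for everyone else: (30 + 240)/500 = 270/500 = 54% right
- Week-6 interviews alone: (15 + 245)/500 = 52% right

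**Possible effect on the pad test, if it were exposed.** The documents give no size for assessor bias, so assume a shift of 25 to 200 ml in every interviewed resident.
- Shift in the mean difference = (30 − 10)/250 × shift = 0.08 × 25 to 0.08 × 200 = 2 to 16 ml
- If all 40 interviewees fall among 344 analysed residents (172 per arm), the multiplier is 20/172 = 0.116, giving about 3 to 23 ml; guessing accuracy is then (30 + 162)/344 = 56%

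Either range is small beside 200 ml.

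**Route to the RRA**
1. Section 4.4 gives the RRA an explaining role, limited to families of residents who cannot be interviewed themselves. If only selected families are approached, that contact reveals selection. If all such families are approached before selection, it reveals nothing. The text fixes neither.
2. Section 12.2 makes the local PI and RRA responsible for local organisation, including consenting. No section sets interview consent apart from this.
3. The RRA also explains the study to staff interviewees, but they are not sampled by residents' allocation, so this route carries no signal.

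The documented role covers only part of the 40. If 25% to 100% of selections reached the RRA (an assumed range), 10 to 40 residents would be exposed.

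**Which outcomes**
- Week-6 interviewees: RRA-collected measures at weeks 12 and 18
- Week-12 interviewees: measures at week 18, and at week 12 if the approach comes first
- Primary outcome: only if the approach precedes the week-6 pad collection, an order the protocol does not set

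**The case against.** The strongest reply is that the protocol already separates the roles well enough. The RRA is given no part in selecting or scheduling. A qualitative research assistant does the interviews, and the Trial Office, which holds the allocations, can apply the quota without the RRA. Section 4.4 can also be read as inviting an eligible pool from which interviewees are later sampled. Much of this stands: what is shown is an unguarded step, not a demonstrated breach. It does not close the gap, because the pool reading is not required by the text and nothing withholds the list from RRAs.

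A reader might infer several stronger things that the documents do not support:
- **That interviews are arranged through the RRA.** The stated role is to explain and answer questions, for one group of carers.
- **That selection discloses allocation.** It is a 75% probability for at most 8% of residents.
- **That residents and relatives are unblinded.** Nothing says they are told the ratio, so being interviewed tells them nothing about arm.
- **That the interview is a co-intervention that biases the ratings.** It is an extra contact about continence, held for up to 12% of one arm and 4% of the other, but the documents give no basis for its shifting arm-level results.
- **That the 3:1 mix is an error.** Section 8.1 sets out to explore experiences of TPTNS, and oversampling that arm serves the aim.

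**Conclusion.** The point holds as a minor, cheaply closed gap in protecting the assessor blind. Sections 4.4, 4.5 and 8.2 together allow a blinded assessor to learn a selection that depends on arm, while outcomes are still being collected. At most 40 of 500 randomised residents (8%), about 30 TPTNS and 10 sham, could be affected. For each of them the chance of TPTNS would be 75%, and overall guessing accuracy about 54%.

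These are upper bounds. They need all 40 interviews, one resident each, and an RRA who knows both the ratio and every selection. They also assume that the 3:1 share holds among the interviews the RRA hears about, since the protocol sets it only over resident and family interviews as a whole.

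The exposure falls mainly on RRA-assisted secondary outcomes at weeks 12 and 18. The documents do not support a claim that the week-6 primary result is compromised: that needs an approach before the visit, and the outcome is a weight. The sample size is unaffected.

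**What to change.** 1. In section 4.4, have the Trial Office qualitative researcher, not the RRA, approach, explain to and consent resident and family interviewees.
2. State there, or in section 8.2, that the interview list is withheld from RRAs.
3. In section 8.2, state that approach and interview at weeks 6 and 12 take place only after that time point's outcome measures are complete.

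The 3:1 mix can stay once selection is concealed. Sampling 1:1 would also remove the signal, but at 40 interviews it would mean 20 from the TPTNS arm instead of 30, which works against the aim in section 8.1 and is not needed.

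The cost is a protocol wording change and a little more contact work for the qualitative researcher, with no new staff. An RRA may still hear of an interview by chance on site, so the change reduces the risk without removing it.
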